### Sample size

We conducted a priori stochastic simulation and estimation to determine the appropriate sample size for our study. Assuming a 30% coefficient of variation (%CV) in drug exposure, we estimated that enrolling 40 participants per antibiotic would provide sufficient power to detect a 30% effect of HIV co-treatment on antibiotic exposure. In alignment with the ICH E9 guidelines on statistical principles for clinical trials and considering an anticipated 10–15% attrition rate due to study withdrawal and loss to follow-up, we increased the sample size by 10 participants per antibiotic. This adjustment results in a total of 50 participants per antibiotic, or 200 participants overall.

For intravenous antibiotics (ceftriaxone) and anti-TB drugs (rifampicin and isoniazid), we assumed a lower %CV of 25% in drug exposure. Based on this assumption and accounting for an anticipated 15% withdrawal rate, we estimate that a sample size of 25 participants will be sufficient to maintain the power needed to detect possible significant changes in drug exposure due to concomitant antiretroviral therapy.

Therefore, the total sample size for this study is 200 participants.

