### Study participants

Participants will be included if they fulfil the following criteria:

**
*Inclusion criteria*
**

1. A personally signed and dated informed consent document2. An adult of 18 years and above living with HIV3. Patients being initiated on or currently receiving antibiotics which may include: amoxicillin (+/- clavulanic acid), azithromycin, ciprofloxacin, rifampicin, isoniazid, ceftriaxone4. Participants who are willing and able to comply with scheduled visits, treatment plan, laboratory tests, and other study procedures.

**
*Exclusion criteria*
**

1. Patients who discontinue antibiotics for any reason following initiation2. Patients receiving antibiotics only for prophylaxis

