### Statistical analysis

**
*Analysis of data on antimicrobial drugs: sparse pharmacokinetic data*
**

Sparse pharmacokinetic data for antimicrobials will be analysed as medians with standard deviations. We assess for the effect of covariates like age, sex, body-mass index, CD4 cell counts on drug concentrations

**
*Analysis of data on antimicrobial drugs: intensive pharmacokinetic data*
**

Non-linear mixed-effects models will be used to calculate the pharmacokinetic parameters of the drugs and this will include the maximum plasma concentration (Cmax), time to maximum plasma concentration (Tmax), and area under the plasma concentration-time curve (AUC). We will also explore the effects of covariates like age, sex, concomitant medications, and body-mass index on the pharmacokinetic parameters.

**
*Pharmacodynamic parameters*
**

We will use pharmacokinetic and pharmacodynamic models to assess the effect of the pharmacokinetic parameters on clinical response. For sparse pharmacokinetic data, we will use drug concentrations as a covariate in the linear regression models predicting clinical response. Clinical response will be defined as either clinical cure (resolution of symptoms) or clinical failure (lack of improvement in signs and symptoms of infection or recurrence of signs/symptoms of infection after initial improvement or death considered at least possibly due to the infection.

**
*Analysis of data on anti-tuberculosis drugs*
**

For participants on anti-tuberculosis drugs, we will evaluate whether dose adjustment leads to the achievement of therapeutic targets.

As an exploratory objective, using Kaplan Meier survival analysis, time to sputum culture negativity will be compared for those who received dose adjustment and those who did not receive dose adjustment within this study. We will also utilize the SOUTH dataset where drug concentrations of rifampicin and isoniazid were measured (without dose adjustment), where 78% and 84% of participants had rifampicin and isoniazid concentrations below the therapeutic targets respectively.

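### The sample size claims power for a 30% effect of HIV co-treatment that the design does not secure, the 25-participant groups do not match the power of the 40, and one sentence on the total contradicts the rest

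*Protocol article*

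**What the plan says.** For the antibiotics, the Sample size section of the protocol article starts from "Assuming a 30% coefficient of variation (%CV) in drug exposure" and continues "we estimated that enrolling 40 participants per antibiotic" "would provide sufficient power to detect a 30% effect of HIV co-treatment on antibiotic exposure". It reports that the number came from stochastic simulation and estimation. It then allows for dropout: "considering an anticipated 10–15% attrition rate due to study withdrawal and loss to follow-up, we increased the sample size by 10 participants per antibiotic". The paragraph closes with "This adjustment results in a total of 50 participants per antibiotic, or 200 participants overall".

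For ceftriaxone, rifampicin and isoniazid it takes a CV of 25% and 15% withdrawal, and states that "a sample size of 25 participants will be sufficient to maintain the power needed to detect possible significant changes in drug exposure" caused by concomitant ART. The section ends by giving 200 as the study total.

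Neither paragraph states a significance level, a power value, a scale, a direction, a comparator or a split. The second gives no effect size.

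Elsewhere in the article:
- The inclusion criteria require "An adult of 18 years and above living with HIV". Being on or off ART is not a criterion.
- Study design describes an observational cohort with 50 on each of three oral drugs (amoxicillin, azithromycin, ciprofloxacin). ART regimens are recorded at baseline.
- Statistical analysis says of the sparse data: "We assess for the effect of covariates like age, sex, body-mass index, CD4 cell counts on drug concentrations". Concomitant medications are named as a covariate to explore in the intensive data.

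**The concern.** Power to detect an effect of co-treatment presupposes people with and without that co-treatment, or on different forms of it, in numbers the design controls. Here the population has HIV throughout, the oral-drug groups come from a clinic providing HIV care, and nothing fixes how many participants fall on each side of an ART contrast. If very few are off ART, or on the regimen of interest, the study could report no visible ART effect alongside a statement that it had sufficient power to see one. The Introduction says that clinical PK studies of the azithromycin interaction it describes are lacking, so a null result could carry more weight than it deserves.

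Two further statements in the same section need checking: that groups of 25 keep the power, and that 50 per antibiotic makes 200.

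**Working it through.** **Inputs from the article (Sample size).** Effect 30%; CV 30% with 40 evaluable for the oral drugs; CV 25%, 25 enrolled and 15% withdrawal for ceftriaxone and the TB drugs.

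**Assumptions, because the article gives none.** Two-sided 5%; one exposure value per person; two-group t-test. The main case is the log scale with a 30% increase; a 30% decrease and the raw scale are shown as variants.

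**1. Reproducing the 40.** The log SD is √ln(1 + CV²): √ln 1.09 = 0.294 at CV 30%, and √ln 1.0625 = 0.246 at CV 25%. The effect is ln 1.3 = 0.262. With 80% power and equal groups, the normal approximation gives

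n per group = 2 × (1.960 + 0.842)² × 0.294² / 0.262² ≈ 19.7, rounded up to 20, so 40 in total.

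This matches the stated 40 exactly, but as a comparison of 20 against 20. Other settings give other totals: 32 (raw scale, 80%), 44 (raw scale, 90%), and 22 or 30 (log scale, 30% decrease, 80% or 90%). The match is therefore suggestive and does not prove how the number was obtained. Dropout is covered: 40/0.90 = 44.4 and 40/0.85 = 47.1, both under 50.

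**2. What the split does.** Power comes from the noncentral t with noncentrality effect / (SD × √(1/n₁ + 1/n₂)). For the log-scale increase this is 0.262/(0.294 × √0.1) = 2.83 at 20/20, and 0.262/(0.294 × √(1/4 + 1/36)) = 1.70 at 36/4.

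| Split of 40 (assumed) | 30% increase | 30% decrease |
|---|---|---|
| 20/20 | 79% | 96% |
| 28/12 | 71% | 93% |
| 32/8 | 60% | 85% |
| 36/4 | 38% | 61% |
| 38/2 | 23% | 37% |
| 40/0 | not estimable | not estimable |

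The normal approximation gives 81% rather than 79% at 20/20, and 40% rather than 38% at 36/4.

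**3. The 25-participant groups.** At a fixed effect and split, the required n scales with the variance:

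40 × (25/30)² = 27.8, so 28 evaluable; 28/0.85 = 32.9, so 33 enrolled.

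Using log variances instead gives 28.1, which is the same to within rounding. The plan has 25 × 0.85 = 21.25, about 21 evaluable. Power with as even a split as possible:

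| Scale and direction (assumed) | 40 evaluable, CV 30% (20/20) | 21 evaluable, CV 25% (10/11) |
|---|---|---|
| Log, 30% increase | 79% | 64% |
| Raw, 30% | 87% | 74% |
| Log, 30% decrease | 96% | 88% |

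The smaller group is lower in every row. Whether it falls below 80% depends on the row.

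**4. The total.** 4 × 50 = 200 is what the sentence on 50 per antibiotic implies. The next paragraph gives 25 for ceftriaxone and for the TB drugs, and Study design gives 50 to three oral drugs only. 3×50 + 25 = 175; 4×50 + 25 = 225; 3×50 + 25 + 25 = 200. Only the last agrees with both the groups of 25 and the stated total.

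**5. What the sample does deliver.** The 95% CI for a geometric mean is exp(± t × SD/√n).
- 40 evaluable, CV 30%: 2.023 × 0.294/√40 = 0.094, giving 0.910 to 1.098, or about −9% to +10%.
- 21 evaluable, CV 25%: 2.086 × 0.246/√21 = 0.112, giving 0.894 to 1.119, or about −11% to +12%.

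**The case against.** **A contrast may still arise.** A reader might infer that an ART effect cannot be estimated at all. The article does not support that. ART is not an entry criterion, regimens are recorded at baseline, and the Introduction frames part of the interaction question by regimen (ritonavir-boosted protease inhibitors). A contrast off ART, or between regimens, could occur. What stands is that its size is uncontrolled, so the power is not secured.

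**The groups of 25 may be adequately powered.** A reader might also infer that they fall below a promised power. No power figure or effect size is given for them. On the raw scale at 80% power, 22 evaluable are needed, and 22/0.85 = 25.9, so 26 enrolled, close to 25. Against a fixed reference value, power exceeds 99% for both group sizes. So only the relative point stands: to keep the power is a comparison with the preceding paragraph, and at an equal effect and split 25 enrolled does not do it.

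**The method differs.** The authors used simulation and estimation with mixed-effects models, and the simulation inputs may be in the full protocol. A t-test on one value per person is a simplification. But no model creates a comparison group that the design does not secure.

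**The covariate list is illustrative.** The absence of ART from the sparse-data covariates is not an error, since the wording marks the list as examples. Nor should the 20 intensive participants per oral drug be judged by this power claim; they have their own precision target.

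**No ART hypothesis test is planned.** ART effect is neither an objective nor an endpoint. That limits the consequence, but it also means the power statement describes an analysis the article does not set up.

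**Conclusion.** The point holds in this form. The claim of sufficient power for a 30% effect of HIV co-treatment cannot be asserted, because the study enrols only people living with HIV and secures no contrast by ART status or regimen. Under the assumptions in the working (log scale, two-sided 5%, 30% increase, CV 30%), 40 evaluable participants give about 79% if split evenly and 38% if split 36/4; the splits are assumptions, as the article gives no ART shares. The groups of 25 do not match the power of the 40 at the same effect and split: about 28 evaluable or 33 enrolled would be needed, against about 21 evaluable. An absolute shortfall below 80% is not established. The sentence tying 50 per antibiotic to 200 overall contradicts the groups of 25. This last finding needs no assumption, and the total of 200 is itself consistent with 3×50 + 25 + 25.

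**What to change.** No extra patients are needed; the changes are to wording and to one covariate.

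1. Replace or qualify the power claim with the precision the sample delivers: a 95% CI for the geometric mean of about −9% to +10% with 40 evaluable at CV 30%, and about −11% to +12% with 21 at CV 25%. Keep a record of how the numbers were originally chosen, so that the new statement is not mistaken for the original rationale.
2. Delete the statement that 25 participants keep the power.
3. Label any ART or between-regimen contrast exploratory, report it with its confidence interval and the numbers on each side, and use the ART regimen already recorded as a covariate for all participants on each drug.
4. State the total as 3×50 oral + 25 ceftriaxone + 25 TB = 200, and remove the sentence that gives 50 per antibiotic as 200 overall.

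The cost is that the stated property becomes less favourable: the article would promise precision in describing exposure, and no assured power for an ART effect.

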^. While it remains unclear to what extent suboptimal drug exposures directly contribute to these resistance patterns, previous studies have reported inadequate antibiotic concentrations to drive development of AMR
^
10
^. Other drivers of AMR include genetic mechanisms which also play a significant role in the emergence and spread of resistance to antimicrobials
^
15
^.

Despite the potential contribution of inadequate drug exposure to AMR, the pharmacokinetic (PK) profiles of commonly prescribed antibiotics in PLWH are not well characterized. Ceftriaxone and amoxicillin may not exhibit significant DDI with ART but some ARVs like ritonavir-boosted protease inhibitors can inhibit transporters like p-glycoprotein and multi-drug resistance protein 2, potentially increasing azithromycin exposure and raising the risk of arrythmias
^
16
^. However, no clinical PK studies have been conducted to investigate these potential interactions, and dose adjustments are not currently recommended.

Therapeutic drug monitoring (TDM) uses plasma drug concentrations to assess whether a given dose achieves optimal drug exposure
^
17
^. It helps evaluate attainment of PK targets for the antibiotics and provides objective data to guide dosing decisions. These PK targets are often based on drug exposure parameters like the area under the concentration-time curve (AUC) or peak/trough concentrations relative to the minimum inhibitory concentration (MIC) of the pathogen. For example, azithromycin and ciprofloxacin require AUC/MIC ratios of ≥5
^
18
^ and ≥125
^
19
^, respectively, while ceftriaxone has a minimum threshold of 8 mg/L
^20^. Amoxicillin efficacy depends on maintaining concentrations above the MIC for at least 40% of the dosing interval
^
21
^. However, MIC testing is rarely done in resource-limited settings due to cost constraints. For important ant-TB drugs like isoniazid and rifampicin, peak plasma concentration of 3 to 6 mg/L and > 8 mg/L are desired, respectively
^
17
^.

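### The sample size section claims power for an antiretroviral effect on drug exposure, but the design plans no comparison group, regimen split or external reference that would secure that power

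*Protocol article*

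**What the plan says.** The Sample size section opens with the method: "We conducted a priori stochastic simulation and estimation to determine the appropriate sample size for our study". For the oral antibiotics it continues "Assuming a 30% coefficient of variation (%CV) in drug exposure", and then "we estimated that enrolling 40 participants per antibiotic" "would provide sufficient power to detect a 30% effect of HIV co-treatment on antibiotic exposure". Ten participants per antibiotic are added for attrition of 10–15%, giving 50. For ceftriaxone and the anti-TB drugs it assumes a CV of 25% and 15% withdrawal, and judges 25 participants enough "to maintain the power needed to detect possible significant changes in drug exposure due to concomitant antiretroviral therapy". It states no alpha, power, direction of effect, reference group or split.

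Elsewhere in the protocol article:

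- **Population.** Eligibility (Study participants) requires "An adult of 18 years and above living with HIV". Antiretroviral treatment is neither required nor excluded.
- **Recruitment.** Study design enrols one group of 50 per oral drug. Nothing is stratified or balanced by antiretroviral status or regimen. Regimens are recorded at baseline.
- **Analysis.** Under Statistical analysis, concomitant medications are a named covariate for the intensive pharmacokinetic data, where covariate effects are to be explored. Those data come from 20 participants per oral drug. The covariates given as examples for the sparse data are age, sex, body-mass index and CD4 count.
- **Objectives and outcomes.** None states a comparison by antiretroviral status.

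**The concern.** Power is a property of a contrast. To detect an effect of co-treatment on exposure, a study needs participants with and without it, two regimens to compare, the same people sampled on and off treatment, or a stated external reference. The protocol article plans none of these. The number in the smaller group is therefore left to whoever happens to be enrolled, and that number drives the power.

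The sample size is justified by this claim alone, apart from the separate precision argument for the 20 intensive profiles. If the claim is not secured, the stated reason for 40 (50 enrolled) and for 25 does not support the numbers. A reader of the results would also lack a sound basis for judging how informative an absent antiretroviral effect is. The aim of describing concentrations and the therapeutic drug monitoring aim do not depend on this contrast.

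**Working it through.** **Inputs from the Sample size section.** CV 30% with 40 evaluable (oral drugs); CV 25% with 25 enrolled and 15% withdrawal, so 25 × 0.85 = 21.25, about 21 evaluable; effect 30% (oral drugs). From the intensive sampling section: 20 per oral drug.

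**Assumptions, because the document gives none.** Two-sided alpha 5%; comparison of log exposure between two groups; effect taken as a ratio of 1.3 or 0.7; the same 30% effect applied to the 25-participant cohorts; the splits themselves.

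**Step 1: can the stated 40 be reproduced?** Not strictly, because alpha, power, reference and split are missing. On the log scale, SD = √ln(1 + CV²) = √ln(1.09) = 0.294. With the normal approximation at 80% power, n per group = 2 × [(1.960 + 0.842) × 0.294 / ln 1.3]², with ln 1.3 = 0.262. This gives 19.7, so 20 per group and 40 in total. For a ratio of 0.7 (|ln 0.7| = 0.357) it gives 10.6, so 11 per group and 22 in total. Thus 40 is consistent with 20 on and 20 off co-treatment, a split that the design does not recruit. The agreement rests on assumed alpha and power and does not show how the simulation was done.

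**Step 2: attrition.** 40/0.90 = 44.4 and 40/0.85 = 47.1, so 45 to 48 enrolled. Fifty covers this, and attrition is not the problem.

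**Step 3: power by split.** Non-centrality = |ln ratio| / [SD × √(1/n₁ + 1/n₂)], with power from the non-central t on n₁ + n₂ − 2 degrees of freedom. Example for 20:20 and ratio 1.3: 0.262 / (0.2936 × 0.3162) = 2.83, critical t = 2.024, power 79%. For CV 25%, SD = √ln(1.0625) = 0.246.

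| Set | Split | Power, 30% increase | Power, 30% decrease |
|---|---|---|---|
| 40 evaluable, CV 30% | 20:20 | 79% | 96% |
| | 30:10 | 66% | 90% |
| | 36:4 | 38% | 61% |
| | 38:2 | 22% | 37% |
| 21 evaluable, CV 25% | 11:10 | 64% | 88% |
| | 18:3 | 37% | 60% |
| | 19:2 | 28% | 46% |
| 20 intensive, CV 30% | 10:10 | 47% | 73% |
| | 18:2 | 21% | 34% |

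If everyone enrolled is on the same co-treatment, the effect cannot be estimated.

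**Step 4: what a single group does deliver.** The 95% CI for a geometric mean has log half-width t × SD/√n.

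- n = 20, CV 30%: 2.093 × 0.2936/√20 = 0.137, i.e. −13%/+15%.
- n = 40, CV 30%: 2.023 × 0.2936/√40 = 0.094, i.e. −9%/+10%.
- n = 21, CV 25%: 2.086 × 0.2462/√21 = 0.112, i.e. −11%/+12%.

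The stated CVs are for drug exposure. Full profiles are planned in 20 participants per oral drug. The primary antibiotic endpoint is the trough concentration, for which no CV is given.

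**The case against.** The best defence is that a contrast does exist. Antiretroviral treatment is not an eligibility condition, regimens are recorded, concomitant medications enter the mixed-effects model, and a between-regimen comparison needs no untreated or HIV-negative group. The number came from simulation and estimation, whose model and assumed regimen mix an article may leave to the full protocol. The two-sample calculation is a stand-in for that simulation, so it illustrates the dependence on the split and does not refute the 40.

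Much of this stands, and it rules out several stronger readings that a reader might infer:

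- *That no comparison is possible.* The documents do not support this. An incidental contrast by status or regimen may arise.
- *That the untreated share will be small.* No antiretroviral coverage or regimen distribution is given, and the ceftriaxone cohort comes from hospital in-patients, so the clinic setting does not settle it.
- *That there is nothing to detect for some drugs.* The Introduction does say "Ceftriaxone and amoxicillin may not exhibit significant DDI with ART", but it goes on to a possible azithromycin interaction and to the lack of clinical studies of such interactions. An expected small effect also says nothing about whether a comparator exists.
- *That a null result will be reported as excluding a 30% effect.* The plan says only that covariate effects will be explored.

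What the defence does not answer is that the missing split is a feature of the eligibility and recruitment text, not merely an omitted simulation detail. An analysis plan cannot supply a comparison group that recruitment does not plan. The SOUTH data do not fill the gap: they come from TB-HIV coinfected patients, cover rifampicin and isoniazid only, and are cited in relation to dose adjustment.

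**Conclusion.** The concern holds in this limited form: the power claimed for an effect of HIV co-treatment or antiretroviral therapy is not secured by the design. Any such contrast is incidental and its split uncontrolled.

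With 40 evaluable, power for a 30% increase comes close to 80% only near an even split. For a 30% decrease it stays at 90% or more down to 30:10, then falls to 61% at 36:4. With 21 evaluable, even a balanced split gives 64% for an increase, against 88% for a decrease. In the intensive set, where concomitant medication is a named covariate, power stays below 80% in either direction even at 10:10. The covariate list for the sparse data is given as examples, so antiretroviral treatment could be added there, but the uncontrolled split would remain.

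These figures rest on the assumed alpha, log-scale two-group comparison, effect direction and splits. They do not show that 40 is the wrong number, only that the reason given for it is not supported. The point should be corrected, but it does not undermine the descriptive or drug-monitoring aims.

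**What to change.** Replace both power sentences in the Sample size section with the precision that one group per drug delivers:

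- Geometric mean exposure from the 20 fully profiled participants per oral drug, CV 30%: 95% CI about −13%/+15%.
- About −9%/+10% for 40 evaluable, only for a quantity measured in all 40 with a CV of 30%. The CV of the trough concentration should be stated as an assumption before this is applied to the primary endpoint.
- About −11%/+12% for 21 evaluable at CV 25%, on the same condition.

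If an antiretroviral contrast is kept, name the groups or regimens compared (or the external reference), give the expected split, alpha and resulting power, and label it exploratory.

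The cost is a rewritten paragraph and a more modest stated claim. No extra participants are needed.

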**Primary endpoints**

Pharmacokinetic parameters

Trough concentrations (Ctrough) for amoxicillin, ciprofloxacin, azithromycin and ceftriaxone

Pharmacodynamic parameters

Clinical response to antibiotics through the time of treatment will be assessed. Clinical response is either clinical cure (resolution of symptoms) or clinical failure (lack of improvement in signs and symptoms of infection OR recurrence of signs/symptoms of infection after initial improvement.

**
*On TB treatment*
**

Pharmacokinetic parameters

Maximum concentrations (Cmax) and area under the concentration-time curve (AUC) defined as the total exposure for rifampicin, isoniazid

Pharmacodynamic parameters

1. Clinical response will be assessed according to the World Health Organization definitions of cure, completed and treatment failure, which will be extracted from the clinic database.2. Occurrence of adverse drug reactions

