### Participants on anti-tuberculosis treatment

The current tuberculosis (TB) treatment involves fixed dose combinations based on weight bands, including an intensive phase of rifampicin, isoniazid, ethambutol, and pyrazinamide (RHEZ) for 2 months, followed by a continuation phase of isoniazid and rifampicin (HR) for 4 months. Dosing is determined by weight bands, with 3, 4, or 5 tablets of RHZE or HR depending on weight (<55, 55–69, ≥70 respectively). Each tablet contains 150 mg of rifampicin and 75 mg of isoniazid for both combinations. Fixed dose combinations in the intensive phase include concomitant pyrazinamide and ethambutol.

Serum rifampicin and isoniazid concentrations (C2hr, C4hr, C6hr) will be measured in participants when fasting, and following directly observed therapy, after two weeks of treatment (First TDM). Results of blood concentrations will be received within 24–48 hours and assessed to determine if the C
_max_ and AUC is within the therapeutic targets. Sub-therapeutic C
_max_ concentrations are considered less than 8mg/L and 3mg/L for rifampicin and isoniazid, respectively. AUCs for rifampicin and Isoniazid will also be considered and compared with existing published therapeutic ranges
^
22
^. Participants found to have subtherapeutic drug exposures will have dose escalation and be asked to take one additional pill of the drug that did not achieve therapeutic target concentrations (rifampicin, isoniazid or both) (
Table 3). A second blood draw for measurement of drug concentrations will be performed after another two weeks (Second TDM) and dose adjustment performed again based on the guidance in
Table 3, if concentrations are still below the target. (
Figure 1)

**Table 3. T3:** Dose adjustment table for isoniazid and rifampicin in patients with HIV.

Weight band	Normal drug levels	Sub-target INH <3mg/dl Normal RIF	Normal INH Sub-target RIF <8mg/dl	Sub-target INH <3mg/dl and Sub-target RIF <8mg/dl
<55kg	Continue INH 225 mg and RIF 450 mg (3 FDCs)	Give an additional INH tablet equivalent to: INH 300 mg	Give an additional rifampicin tablet equivalent to 600 mg dose	Give additional rifampicin and isoniazid tablets or FDCs equivalent to 300 mg INH and 600 mg rifampicin

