**Figure 1. f1:**
[figure not shown]
Therapeutic drug monitoring procedure with dose adjustment for participants on TB drugs.

If the participant is still not achieving the therapeutic target concentrations after the second C
_max_, another 1hr and 6hr blood draw will be conducted to assess for the presence of fast or delayed absorption. An additional dose adjustment with 1 additional tablet of the respective drug may be prescribed for these patients at the discretion of the study team and with consideration of observed side effects, treatment response, and concentrations attained. Those who attain therapeutic drug concentrations during TDM will revert to the previous dose. The final doses provided will be recorded for all participants.

**
*Sputum analysis*
**

For participants with tuberculosis, sputum cultures will be conducted at the Makerere University Microbacteriology laboratory. Cultures using Mycobacterium Growth Indicator tube (MGIT) and Lowenstein-Jensen (LJ) agar will be conducted within 7 days of enrolment and will be conducted every two weeks for the first eight weeks of TB treatment (intensive phase).

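### The claim that 25 participants keep the power for rifampicin and isoniazid does not follow from the protocol's own figures, and it rests on an unsourced 25% CV shared with intravenous ceftriaxone

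*Protocol article*

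**What the plan says.** The Sample size section of the protocol article makes two calculations.

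- **General calculation.** "Assuming a 30% coefficient of variation (%CV) in drug exposure, we estimated that enrolling 40 participants per antibiotic would provide sufficient power". The effect in view is a 30% change in exposure attributed to HIV co-treatment. The 40 is raised to 50 for attrition. Under Study design, 50 is the target for each of amoxicillin, azithromycin and ciprofloxacin.
- **Ceftriaxone and the TB drugs.** "For intravenous antibiotics (ceftriaxone) and anti-TB drugs (rifampicin and isoniazid), we assumed a lower %CV of 25% in drug exposure". With 15% withdrawal, "we estimate that a sample size of 25 participants will be sufficient to maintain the power needed" to find changes in exposure due to antiretroviral therapy (ART). The effect size is not restated here. No source is given for the 25%.

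The stated total of 200 fits 3 × 50 + 25 + 25, so I read 25 as the size of the TB cohort.

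Rifampicin and isoniazid are given by mouth, "with 3, 4, or 5 tablets of RHZE or HR depending on weight". Both Cmax and AUC are TB endpoints, and the numerical thresholds for dose adjustment are set on Cmax. For participants still below target after the second round of monitoring, "another 1hr and 6hr blood draw will be conducted to assess for the presence of fast or delayed absorption". The Statistical analysis section also plans to use the SOUTH data, which hold rifampicin and isoniazid concentrations measured without dose adjustment.

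**The concern.** The 25% CV and the withdrawal rate are the only stated grounds for a TB cohort half the size of each oral-antibiotic cohort. The same CV covers an intravenous drug and two oral ones, and nothing in the text supports it for the oral pair. The protocol itself allows for irregular absorption in some TB participants, which bears directly on Cmax. A dataset that could supply the CV is already part of the plan.

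At stake is how a null result is read. If the report repeats that 25 participants gave adequate power, failure to see an ART effect on rifampicin or isoniazid could be taken as evidence of no interaction. The cohort may have had little better than an even chance of seeing a 30% effect.

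**Working it through.** **Inputs from the Sample size section:** 40 evaluable at CV 30% for a 30% effect; CV 25%, 25 enrolled and 15% withdrawal for the TB drugs.

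**Assumptions, because the article does not state them:** two-sided 5%, 80% power as the reference, two near-equal groups, exposure analysed on the log scale, and the 30% effect taken as a ratio of 1.3 and carried over to the TB cohort. The protocol used simulation and estimation, so these are approximations to it.

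**Step 1. The withdrawal step.** 25 × 0.85 = 21.25, so about 21 evaluable. In reverse, 21/0.85 = 24.7, so 25. This step is consistent.

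**Step 2. Reproduce the 40.** SD on the log scale = √ln(1 + CV²), which is 0.294 at CV 30% and 0.246 at CV 25%. The number per group is 2(1.96 + 0.84)² × SD² / (ln 1.3)².

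- CV 30%: 2 × 7.85 × 0.0862 / 0.0688 = 19.7, so 20 per group and 40 in total. This matches the protocol.
- CV 25%: 2 × 7.85 × 0.0606 / 0.0688 = 13.8, so 14 per group and 28 in total. With 15% withdrawal, 28/0.85 = 32.9, so 33 enrolled. The protocol states 25.

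**Step 3. The same result by scaling alone.** If effect, power, significance level and split are held fixed, the required number scales with the squared CV: 40 × (25/30)² = 27.8, about 28 evaluable. This does not depend on which significance level, power or split was chosen. The lower CV therefore accounts for a fall from 40 to 28, but not to 21.

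**Step 4. Power with 21 evaluable.** Two-sample noncentral t, 19 degrees of freedom, noncentrality ln 1.3 / (SD × √(1/11 + 1/10)).

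| CV | Log SD | Noncentrality (11 v 10) | Power, 11 v 10 | Power, 17 v 4 | Ratio detectable at 80% power, 11 v 10 |
|---|---|---|---|---|---|
| 25% | 0.246 | 2.44 | 64% | 44% | 1.37 |
| 30% | 0.294 | 2.04 | 49% | 33% | 1.46 |

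By the same method, the protocol's 40 at CV 30% (20 v 20) give 79%. The 17 v 4 split is an assumed example of unequal ART groups.

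**Step 5. Other scales.** On the arithmetic scale (difference 0.30, SD equal to the CV), power with 21 evaluable is 74% at CV 25% and 58% at CV 30%. That scale gives 22 evaluable, or 26 enrolled, at CV 25%, which is close to 25. At CV 30%, however, it gives 32, not 40. Log and arithmetic scales, a ratio of 0.7, the CV used directly as the log SD, and 80, 85 or 90% power were tried. No combination returned both 40 and 25.

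**The case against.** A reader might infer that 25% is simply wrong, because the only ground for a lower CV is the intravenous route and the protocol uses 30% for oral drugs. The documents do not support that. The Sample size section gives no reason for 25%, so there is no stated reason to refute. It does not label 30% an oral value; that is inferred from where the 50 is applied. Different planning CVs for different drugs are not a contradiction. Weight-band dosing, fasting and observed intake could reduce variability in the TB cohort, although the article does not argue this. The CV is one of drug exposure, and irregular absorption affects Cmax more than AUC. The extra draws are a contingency for some participants and say nothing about the CV across the cohort. All of this stands.

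A second objection is that the simulation is not shown and may differ from a two-group test. TB participants have three samples per occasion on at least two occasions, so each may contribute more information than a sparsely sampled participant on an oral antibiotic. The 40 may also have been more than the minimum. A condensed article may properly leave the model and its sources to the full protocol. This limits what can be proved: 25 can be neither confirmed nor refuted exactly. But the article prints the CV, the size and the power claim, and it bases the claim on the CV and withdrawal alone. On those grounds the claim does not follow.

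Third, the Statistical analysis section describes the TB analysis as attainment of targets after dose adjustment and names no ART comparison for these drugs. A planning CV also does not bias an estimated effect or its interval. Both points are right, and they keep the consequence modest: what is overstated is the study's ability to detect an ART effect, not the effect itself.

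**Conclusion.** The statement that 25 participants keep the needed power is not supported as written. On the protocol's own 40 at CV 30%, the move to CV 25% calls for about 28 evaluable (33 enrolled), against about 21 planned. The statement is also sensitive to the CV: about 64% power at 25% and 49% at 30%, with detectable ratios of 1.37 and 1.46. The scaling assumes the same effect, power and split in both calculations. The power figures also assume a two-sided 5% test, the log scale, a ratio of 1.3 and near-equal groups, and they fall with an unequal ART split.

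It would go too far to say that the CV is shown to be wrong, or that it alone explains the halved cohort: the shortfall exists even if 25% is accepted. Power at CV 40% (32%) or 50% (23%) is illustrative only, since the documents give no such values.

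**What to change.** Keep the 25 participants and amend the Sample size section as follows.

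1. Treat rifampicin and isoniazid separately from ceftriaxone.
2. Take the between-participant CV of AUC and of Cmax for each TB drug from the SOUTH dataset, if it is available in a form that allows this, and cite it. Otherwise show results at both 25% and 30%.
3. Replace the power claim with the effect detectable at 80% power, stating the significance level and the assumed ART split. On the assumptions used here: *with about 21 evaluable participants in two near-equal groups and a two-sided 5% test on the log scale, the detectable difference in exposure is about 37% at CV 25% and 46% at CV 30%; it is larger if the groups are unequal.*

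The cost is one descriptive calculation on data already in the plan and a reworded sentence. No participants are added and no clinical procedure changes. The downside is a less favourable stated figure.
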